# Study protocol for testing the efficacy of the Helping Educational Leaders Mobilize Evidence (HELM) implementation strategy in elementary schools: a hybrid type 3 effectiveness-implementation randomized controlled trial

**DOI:** 10.1186/s13012-025-01429-4

**Published:** 2025-04-24

**Keywords:** Schools, Implementation leadership, Implementation climate, Implementation strategy, Prevention

## Abstract

**Background:**

Schools need to implement universal student supports that prevent social, emotional, and behavioral difficulties; minimize associated risks; and promote social, emotional, and behavioral competencies. The purpose of this study is to examine the efficacy of the Helping Educational Leaders Mobilize Evidence (HELM) implementation strategy for promoting school-level implementation leadership, implementation climate, and high-fidelity delivery of an evidence-based practice. We will test HELM with an exemplar EBP, Positive Behavioral Interventions and Supports (PBIS). The specific aims of the study are to: 1) experimentally evaluate the effects of HELM versus PBIS training and technical assistance only (control condition); and 2) explore for whom, under what conditions, how equitably, and through which processes HELM works to improve outcomes, as well as its cost-effectiveness.

**Methods:**

This study will use a hybrid type 3 effectiveness-implementation trial to provide a rigorous test of the effects of HELM in elementary schools. Schools will be randomly assigned to HELM + PBIS training and technical assistance (*n* = 21 schools; n = 210 educators) or PBIS training and technical assistance only (*n* = 21 schools; n = 210 educators) in a 1:1 ratio within cohorts using covariate constrained randomization that accounts for degree of prior PBIS exposure (measured using the Tiered Fidelity Inventory at baseline) and school size. A series of mixed effects models (time within educator, educator within school) will test within-subject/between-subject interactions across three timepoints (12 months total) to examine whether HELM will show steeper gains than the control on implementation leadership (primary outcome), implementation climate, PBIS fidelity, and student outcomes. Mediational analyses will test hypothesized mechanisms of change (i.e., implementation leadership and climate) of HELM on PBIS fidelity. Sequential mixed-methods data collection and analyses will further explore how organizational mechanisms are linked to implementation outcomes. Cost-effectiveness analyses will compare costs and outcomes of PBIS training and technical assistance only versus PBIS implementation with HELM.

**Discussion:**

The nature of leadership support in schools can make the difference between successful and unsuccessful EBP implementation. Testing HELM within the context of PBIS implementation will provide rigorous evidence about whether and how HELM can equitably address important EBP and student outcomes.

**Name of the registry:**

clinicaltrials.gov.

**Trial Registration:**

Clinical Trials ID: NCT06586723. Date of Registration: August 27, 2024. Prospectively registered. URL of Trial Registry Record: https://clinicaltrials.gov/study/NCT06586723?intr=helm&rank=1

**Supplementary Information:**

The online version contains supplementary material available at 10.1186/s13012-025-01429-4.

Contributions to the Literature
Few effective strategies to enhance evidence-based practice implementation in schools address implementation leadership and climate, and those that do have only been evaluated qualitatively.Schools have unique organizational characteristics, and it is important to test whether organizational implementation strategies developed in other contexts can be effective in improving implementation outcomes in schools.This study will evaluate the effects of a tailored adaptation of the Leadership and Organizational Change for Implementation (LOCI) strategy for schools, entitled Helping Educational Leaders Mobilize Evidence (HELM), on implementation mechanisms (implementation leadership and implementation climate), PBIS fidelity, and student outcomes.This study also will explore for whom, under what conditions, and how equitably HELM demonstrates its effects, providing critical information about influence on – and the limitations of – the impact of this organizational implementation strategy.Finally, the study will evaluate the processes through which HELM works to improve outcomes, contributing to the emerging literature on implementation mechanisms, as well as its cost-effectiveness.

## Introduction

Social, emotional, and behavioral problems occur frequently among elementary school students and dramatically impede student outcomes [1–3]. Numerous evidence-based practices (EBPs) exist to address student social, emotional, and behavioral needs, prevent problems, and ensure academic success [4]. A recent meta-analysis supports the utility of universal (i.e., “Tier 1”) interventions in improving student social, emotional, and behavioral functioning [5]. One exemplar universal EBP is Positive Behavioral Interventions and Supports (PBIS; [6–8]), a multi-tiered, problem-solving, and team-based continuum of supports that promotes all students’ social, emotional, and behavioral development [8]. Studies indicate that fidelity of PBIS delivery is highly variable across schools and often falls below levels associated with improvements in student functioning [9]. Unfortunately, variable fidelity attenuates the impact of even the most efficacious programs [10] and results that are rarely leveraged to benefit the broader population [11].

Prior research suggests that organizational factors at the level of the school building are associated with successful implementation of EBPs [12–19]. In particular, implementation leadership (i.e., proactive leader behaviors that facilitate EBP use; [20]) and implementation climate (i.e., educator perceptions of whether EBP use is valued, expected, rewarded by the school; [21]) have been repeatedly linked to higher EBP fidelity in elementary schools [13, 17, 22, 23]. Unfortunately, few effective interventions to enhance EBP implementation in schools address these factors and those that do have only been evaluated qualitatively [24].

## Helping educational leaders mobilize evidence (HELM)

To fill the gap in implementation strategies that address organizational factors within schools, our research team recently adapted the evidence-based Leadership and Organizational Change for Implementation (LOCI; [25–30]) strategy for use in the education sector. LOCI is informed by the Exploration, Preparation, Implementation, Sustainment (EPIS) framework, which details influences on implementation success over multiple phases [28]. We used a human-centered design framework [29] to enhance LOCI’s acceptability, feasibility, contextual appropriateness, usability, and effectiveness for public schools [30, 31]. The redesigned strategy – Helping Educational Leaders Mobilize Evidence (HELM) – aims to improve principals’ use of implementation leadership to support the high-fidelity delivery of EBPs that improve child outcomes [32]. HELM was designed so that it can be flexibly applied to support the implementation of any universal EBP.

The HELM theory of change (Fig. 1) model depicts the HELM core components, hypothesized organizational mechanisms, implementation outcomes, and student outcomes. Identification of implementation mechanisms is critical to developing effective and streamlined implementation strategies [27–29, 33–36]. The theory of change posits that HELM will improve school implementation leadership and climate [20, 21], which leads to higher-fidelity implementation of PBIS, which then leads to improved student social, emotional, and behavioral outcomes such as disciplinary referrals [15].

**Fig. 1 Fig1:**
[figure not shown]
HELM Theory of Change

## Preliminary HELM studies

Previous research found that implementation leadership and climate are malleable constructs and that changes in implementation leadership due to intervention contribute to improvements in implementation climate, EBP adoption, and observed fidelity [22, 37, 38]. Results from these studies validate key organizational mechanisms in HELM’s theory of change.

HELM was iteratively developed using the Discover, Design/Build, Test (DDBT) framework which leverages human-centered design and implementation science to guide adaptation of complex interventions for new users or settings [32]. The initial Discover and Design/Build phases involved 1) focus groups (*N* = 54 educators; 34); 2) expert input (from *N* = 15 implementation researchers and school practitioners) using a nominal group decision making process and “hackathon” solution generation (34); and 3) the Cognitive Walkthrough for Implementation Strategies (CWIS: [39]) method to evaluate HELM usability (i.e., the extent to which an intervention can be used by specified users with effectiveness, efficiency, and satisfaction; *N* = 15 principals; 30). These activities informed iterative adaptations to improve the suitability of HELM for the school context, such as aligning assessment windows to school calendars and prioritizing former school leaders as HELM coaches [31]. Furthermore, a pilot study examined the feasibility of HELM and research procedures for testing it in a large-scale Test phase trial [32]. HELM schools had significantly better implementation leadership and implementation climate (HELM’s organizational mechanisms of change) over time than control schools. Students in HELM schools also demonstrated significant increases in positive behavior compared to those in control schools, such as the extent to which their classroom teachers rated them as following directions the first time when asked (Cohen's f^2^ = 0.84, a large effect size).

## PBIS

The current project aims to test whether HELM can yield school-wide improvement in implementation outcomes and student outcomes when implementing PBIS as an exemplar EBP. PBIS organizes support across multiple tiers of intensity that vary based on the level of student need. The three tiers are: 1) Tier 1: Primary Prevention, where all students receive universal supports to increase social, emotional, and behavioral outcomes to enhance academic success; 2) Tier 2: Secondary Prevention, where some students who have not been successful with Tier 1 support alone and are at an elevated risk for problems receive supplemental support to prevent more challenging behaviors; and 3) Tier 3: Tertiary Prevention, where a few students at high risk or experiencing significant challenges receive individualized support to reduce severity (www.pbis.org). PBIS has demonstrated consistent evidence for its effects including reduced student problem behavior and improved social, emotional, and behavioral functioning in elementary schools [40–44]. PBIS is a school-wide program that integrates: 1) student and school data to identify needed supports; 2) using classroom- and student-level EBPs; and 3) implementing a systems approach designed to support fidelity. In PBIS, the system is the infrastructure (e.g., operational supports to use data) to support educators to successfully implement EBPs, and leadership is an integral part of this system.

## Study purpose and aims

The purpose of this study is to test the effectiveness of HELM on school-wide implementation of PBIS (i.e., fidelity) relative to a PBIS training and technical assistance condition. Experimental and exploratory aims are:

### Aim 1: Experimentally evaluate the effects of HELM.

Hypothesis 1a. Schools randomized to HELM will demonstrate higher PBIS fidelity compared to schools randomized to PBIS training and technical assistance only (control schools).

Hypothesis 1b. Schools randomized to HELM will demonstrate greater improvement in school context factors that support implementation (i.e., implementation leadership, implementation climate) compared to control schools.

Hypothesis 1c. Students in schools randomized to HELM will demonstrate improved social, emotional, and behavioral and academic outcomes compared to students in control schools.

### Aim 2: Explore for whom, under what conditions, how equitably, and through which processes HELM works to improve outcomes, as well as its cost-effectiveness.

Research Question 2a. Are the effects of HELM on PBIS fidelity mediated by improvement in organizational mechanisms of change (i.e., implementation leadership and climate)?

Research Question 2b. Are the effects of HELM on student outcomes mediated via implementation outcomes (i.e., PBIS fidelity)?

Research Question 2c. Are the effects of HELM consistent and equitable across buildings or are they moderated by school contextual factors (e.g., school size, student body racial/ethnic diversity, free/reduced price lunch)?

Research Question 2d. What explains implementation success in schools where HELM’s explanatory model does not fit? What factors outside of the hypothesized mechanisms explain implementation success (i.e., high fidelity) in schools where HELM’s explanatory model does fit?

Research Question 2e. What are the costs and cost-effectiveness of HELM vs. PBIS implementation as usual?

## Method

This study will use a hybrid type 3 effectiveness-implementation trial with a standard PBIS training and technical assistance only control condition to provide a rigorous test of the effects of HELM in elementary schools.

### Participants

Participating schools (*N* = 42) will be recruited into three cohorts (*n* = 14 schools p/cohort) from districts located in Washington state using a stratified recruitment approach. Schools will be compensated $400 total to support time for recruitment, retention, and other research activities. Inclusion criteria for districts are: 1) presence of a district-wide commitment to implement PBIS in elementary schools, as evidenced by either having completed a PBIS training in the past two years from certified coaches or a willingness to complete the training at the outset of study participation; 2) data sharing agreements with the project investigative team (including sharing of administrative data regarding students); 3) commitment to help recruit 10 educators per elementary school to complete study assessments (*N* = 420); and 4) no previous HELM exposure. Principals and leadership teams will participate in HELM for schools assigned to that condition. The research team will invite all educators from the school to participate in surveys and PBIS trainings and contacted by email or phone to complete informed consent. We will gather de-identified school administrative data for students in each classroom with no identifiable information and, therefore, active parental permission is not needed.

*Randomization*. Random assignment will occur at the school building level because both HELM and PBIS are building-level processes. The study methodologist will generate the randomization sequence, with allocation concealed from all other study personnel and participants. We will randomize schools within cohorts with equal probability (1:1) to: 1) PBIS + HELM; or 2) standard PBIS training and technical assistance. We will use covariate constrained randomization that accounts for degree of prior PBIS implementation and school size [45, 46]. Covariate constrained randomization enumerates a large number of possible assignments of the interventions to schools and quantifies the balance across arms with regard to a set of prespecified covariates (i.e. degree of prior PBIS implementation and school size). From a subset of possible assignments that achieve adequate balance, one is randomly chosen as the final allocation of interventions for the study.

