**Fig. 2 Fig2:**
[figure not shown]
HELM mediational model: RQ2a

*Data Analytic Approach*. We will explore for baseline equivalence between conditions on all school, teacher, and student variables following Institute of Educational Sciences guidelines, with effect sizes between 0.05 and 0.25 indicating that statistical adjustment for nonequivalent baseline characteristics is required [73]. Non-equivalent baseline characteristics will be included as covariates at the school, educator, or student level, as appropriate. Following best practice guidelines, variables used for covariate constrained randomization will be included as covariates in all models [46, 74]. Data missing at random will be modeled using full information maximum likelihood estimation in mixed effects modeling or multiple imputation for other analyses. Although all analyses will use an intent-to-treat approach, we will examine the robustness of condition assignment through descriptive analyses of scores on the HELM fidelity tools. Schools that achieve 80% or higher of the maximum possible score on all HELM fidelity criteria will be considered having received a full dose of HELM training and coaching.

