All analyses will use an intent-to-treat approach in which units are analyzed based on condition assignment regardless of HELM implementation success [75]. Because the trial includes outcomes at multiple levels, the specific analytic approach will vary depending on the outcome. However, in general, analyses will employ 2- or 3-level mixed effects models reflecting data collection time points nested within educator/classroom nested within schools. We will test for significantly large ICCs at the district levels to determine if statistical nesting is necessary. Standard model-building procedures will be used [76, 77], including fitting a null model to facilitate calculation of variance accounted for in later models, fitting unconditional growth models (e.g., linear, quadratic, piecewise) to determine the optimal functional form for time, and finally, fitting models that include the variable for condition (and the condition by time interaction, as appropriate) along with covariates. Iterative models with possible covariates will be tested. Covariates not significantly contributing to the model at *p* < 0.10 based on likelihood ratio tests will be removed. We will obtain estimates of whether there were statistically significant differences between conditions on rate of change over time (i.e., slope), and whether there are statistically significant condition differences in average score on each outcome at T2 and T3. Models will be generalized, with appropriate link functions (e.g., log-link, Poisson) applied based on distributional form (e.g., dichotomous, zero-inflation). Estimations will be fit using full maximum likelihood. Models will be assessed for possible violations of assumptions. Inference will be evaluated relative to *p* < 0.05. For hypotheses/research questions with multiple DVs, we will adjust for familywise error using Benjamini and Hochberg’s False Discovery Rate [78].

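### Schools are randomised within three cohorts, but the rule for which design variables enter every model leaves cohort out; if it stays out, the HELM tests are slightly conservative and lose a little power

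*Protocol article*

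**What the plan says.** **Design.** Under Participants, the 42 schools "will be recruited into three cohorts" of 14 each. The Randomization paragraph there says "We will randomize schools within cohorts with equal probability (1:1) to" the two conditions, and the Abstract repeats this. Equal allocation of 14 schools means 7 against 7 in each cohort. The constrained randomisation works on "a set of prespecified covariates (i.e. degree of prior PBIS implementation and school size". Cohort is the stratum within which this is done and is not one of those covariates.

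**Analysis.** Data analysis, Data Analytic Approach, gives four ways for a term to enter a model:

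- Design variables: "variables used for covariate constrained randomization will be included as covariates in all models".
- Baseline characteristics that differ between conditions are added as covariates.
- Levels: "2- or 3-level mixed effects models reflecting data collection time points nested within educator/classroom nested within schools", with a possible further level: "We will test for significantly large ICCs at the district levels to determine if statistical nesting is necessary".
- Other candidate covariates are tried in turn, and those that do not reach p < 0.10 "based on likelihood ratio tests will be removed".

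The tests are of condition differences in slope and in mean score at T2 and T3. Cohort is not mentioned anywhere in this section. The Power Analysis paragraph accounts for time points, educators or classrooms, and schools, and does not mention cohort either.

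**The concern.** Balancing the arms within cohort removes cohort differences from the true error of the HELM contrast, because each cohort contributes equally to both arms. An analysis without cohort still counts those differences as residual between-school variation. The estimated standard error then exceeds the true one, the test rejects too seldom under the null, and power is lost.

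The article states a principle, that design variables belong in the models, and applies it to the two balancing covariates but not to the stratum. Of the other routes, baseline non-equivalence cannot bring cohort in, since 7 against 7 in each cohort leaves no imbalance to detect. The listed levels do not include cohort. The candidate-covariate step could bring it in, but the article neither names it as a candidate nor guarantees that it stays.

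What is at stake is efficiency. A school-level outcome such as the TFI rests on 42 units and has little power to spare. Cohort differences are plausible, because cohorts are recruited as separate groups and HELM group coaching is run by cohort.

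**Working it through.** **Inputs from the article.** 42 schools; three cohorts, 7 v 7 in each; significance level 0.05; school ICC 0.1 to 0.35; 10 to 12 educators per school; pretests explaining 50% of posttest variance; detectable effects 0.23 to 0.65.

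**Assumptions.** Two-sided tests and a power target of 80%. The cohort share v of the between-school variance that remains after the other covariates is not in the article and is varied from 0 to 20%.

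**Step 1: the plan's own figure.** For a school-level outcome, the detectable effect is (t₀.₉₇₅ + t₀.₈₀) × √(4(1 − R²)/J) on J − 2 degrees of freedom, with R² = 0.5.

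- J = 40: (2.024 + 0.851) × √(2/40) = 0.643
- J = 42: (2.021 + 0.851) × √(2/42) = 0.627

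Both agree with the upper end of 0.65, so a school-level outcome sits at the top of the stated range. The lower end is not fully reproduced: ICC 0.1 with 10 to 12 educators gives about 0.26 to 0.28. The article does not give the inputs by outcome. Cohort plays no part in this calculation.

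**Step 2: standard error inflation, school-level outcome.** If cohort makes up a realised share v of the between-school variance, the standard error without cohort is too large by about 1/√(1 − v):

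- v = 5%: 1.026
- v = 10%: 1.054
- v = 20%: 1.118

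**Step 3: educator-level outcome.** Within-school sampling error dilutes the effect. Between-school variance is a fraction λ = ICC/(ICC + (1 − ICC)/n) of the variance of a school mean, and the inflation is 1/√(1 − vλ). With n = 10:

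- ICC 0.1: λ = 0.10/(0.10 + 0.09) = 0.526; inflation 1.013 at v = 5% and 1.057 at v = 20%
- ICC 0.35: λ = 0.35/(0.35 + 0.065) = 0.843; inflation 1.022 at v = 5% and 1.097 at v = 20%

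**Step 4: type I error and power, school-level outcome.** Simulation of 42 schools, 7 v 7 in three cohorts, with cohort effects drawn at random. The effect is set for 80% power when cohort is fitted; 100,000 trials per row.

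| Assumed share | Type I error, no cohort | Power, no cohort | Power, cohort fitted |
|---|---|---|---|
| 0% | 5.0% | 80.2% | 80.1% |
| 5% | 4.6% | 78.9% | 79.9% |
| 10% | 4.3% | 77.8% | 80.0% |
| 20% | 3.7% | 75.2% | 80.1% |

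With cohort fitted, type I error is about 5% in every row. If the share is instead fixed in every trial, as in the formula of step 2, the effect is larger: type I error without cohort is 4.4, 3.9 and 2.9%, and power 78.8, 76.7 and 72.5%. Random effects give smaller figures because three drawn cohort means often lie close together.

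**Step 5: slope tests.** In a separate simulation (40,000 trials), a cohort shift constant over time had no effect: type I error 5.0% and power 80% with or without cohort. Where cohorts differed in trend, a 10% share of school slope variance gave type I error 4.3% without cohort terms against 5.0% with them, and power 80.5% against 82%. A 20% share gave 3.9% against 5.1%, and power 82% against 85%.

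**Step 6: the candidate-covariate route.** When cohort is offered under the p < 0.10 rule in the setting of step 4, it is kept in about 29, 43 and 62% of trials at shares of 5, 10 and 20%. Power is about 80% and type I error about 5% throughout.

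**The case against.** **Silence is not exclusion.** A reader might infer that cohort is excluded from every analysis. The article does not say so. It says that the constrained-randomisation variables go into all models, not that nothing else does; it describes the models in general terms; and the analysis plan is not shown. This stands, and the point is limited accordingly. What remains is that the article does address which design variables enter and leaves out the one it stratifies on.

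**The existing covariate step would repair it.** Step 6 shows that offering cohort under the p < 0.10 rule recovers nearly all the loss. This stands too, so exemption from removal gains almost nothing in power. Its value is that the model is fixed in advance. The loss arises only if cohort is never offered, and the article does not commit to offering it.

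**The size is assumed, and some tests are protected.** This is correct. The share v appears nowhere in the document. A reader might apply the 3 to 12% inflation of step 2 to all outcomes, but it holds only for school-level ones. The school random intercept protects slope tests against constant cohort shifts. For the TFI, the baseline score is already a covariate and absorbs cohort differences in starting level.

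**False positives.** A reader might also take an ignored stratum to inflate type I error. Here the direction is the reverse: arms are balanced within cohort, so the test is conservative.

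**Conclusion.** The point holds in a limited form. The trial randomises within cohort, its rule for design variables omits cohort, and no other stated route guarantees cohort a place. If it is left out, the T2 and T3 comparisons are mildly conservative, and so are slope tests where cohorts differ in trend. For a school-level outcome the cost is about 1, 2 and 5 points of power at assumed shares of 5, 10 and 20%. For educator-level outcomes with 10 per school, the standard error is too large by about 1 to 6% at ICC 0.1 and 2 to 10% at ICC 0.35.

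These figures rest on the assumed cohort share, two-sided testing and an 80% power target. Validity is not threatened. The case for acting is that fitting the stratum costs almost nothing and matches the analysis to the randomisation.

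**What to change.** In Data analysis, Data Analytic Approach, extend the sentence on design variables: cohort (two indicator terms) is included as a fixed effect in all condition models alongside prior PBIS implementation and school size, and cohort-by-time is added in the repeated-measures models. State that these terms are prespecified and not subject to the p < 0.10 removal rule.

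**Cost.** For school-level tests, two degrees of freedom (40 to 38 before other covariates), which is about 0.2 point of power or less if cohorts do not differ. With time as three categories, cohort-by-time adds four further parameters; with linear time, two. The Discussion reports no enrolment as of February 2025, so on that status the change could be made before any data exist.
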